**Fig. 1 Fig1:**
[figure not shown]
SPIRIT schedule of enrollment, interventions, and assessments. IADL instrumental activities of daily living

**Fig. 2 Fig2:**
[figure not shown]
Flow chart of the study procedures. Expectations are the participants’ expectations about benefits in visuospatial cognitive performance. AE adverse event

### Participants

The study aims to include 100 participants who we will recruit via local newspaper articles and flyers. Inclusion criteria are 50 years of age or older, unimpaired cognition defined by a Mini-Mental State Examination (MMSE) [27] score ≥ 24, the commitment to invest at least 1 h per day for 30 days in solving jigsaw puzzles within a 5-week period, an interest in solving jigsaw puzzles, and low jigsaw puzzle experience in the past 5 years (fewer than five completed jigsaw puzzles).

Exclusion criteria are the participation in another interventional study and self-reported, uncorrected impairment in vision (e.g., red-green color blindness) or motor function of the upper extremity (e.g., hand tremor) that considerably impairs jigsaw puzzle performance. In addition, individuals with any self-reported psychiatric, neurological, or other diseases that could affect cognitive change over time will be excluded. These diseases comprise current major depression, dementia or Parkinson’s disease, a history of stroke with current impairment, epilepsy, multiple sclerosis, or a current malignant tumor. Apart from the cognitive impairment, which we will assess at the on-site screening (t_2A_), telephone-based pre-screening will examine inclusion and exclusion criteria after oral informed consent (t_1_, see Figs. 1 and 2).

### Measures

All outcomes of the study are continuously scaled and we will assess the mean change between baseline (t_1_) and posttest assessments (t_6,_ approximately 5 weeks after t_1_). The outcome domains and their specific measurement, and the assessment of participants’ expectations, predictive variables of cognitive decline, and adverse events are described in the following sections.

#### Primary outcome

A composite score of global visuospatial cognition will depict the primary outcome reducing α-error inflation [28]. This score will constitute the average of the eight, *z*-standardized visuospatial cognitive ability scores that include visual perception, visuoconstruction, mental rotation, processing speed, flexibility, working memory, reasoning, and episodic memory (see “Secondary outcomes”). We will calculate the individual composite scores, if at least five cognitive ability scores are available for both pretest and posttest for an individual. Analysis will be based on individuals for whom both pretest and posttest ability scores are available. We will *z*-standardize all test scores based on pretest means and standard deviations.

#### Secondary outcomes

Secondary outcomes of visuospatial cognition will include the eight visuospatial cognitive ability scores. An adapted version of Benton’s Judgment of Line Orientation Test will assess visual perception [29]. In addition to Benton’s 30 original test items, the version in this study will also include five new test items of greater difficulty to differentiate performance in the higher performance range (visual perception score: number of correct items). The Rey Complex Figure Test (pretest) [30] and the Taylor Complex Figure Test (posttest) [31] will serve to evaluate visuoconstruction and visuospatial episodic memory. Pretest and posttest assessments will apply different figures to minimize the risk that recall of the pretest figure affects posttest performance (visuoconstruction score: points in the copy trial; episodic memory score: sum of the points in the immediate and delayed free recall trials; two raters (DL and HA) will rate all trials; points for each trial depict the mean of both ratings). The Mental Rotations Test (MRT)-Letters (12 items; maximum (max.) time: 90 s) adapted from [32] and the MRT-A (items 1–12; max. time: 240 s) [33] will measure 2D and 3D mental rotation performance, respectively, in order to produce a score of mental rotation ability (2D and 3D sub-scores: seconds per correct item; in the case of no correct item, the score will depict twice the max. time; mental rotation score: average of both *z*-standardized sub-scores). The Trail Making Test (TMT) A and B will assess visuospatial processing speed and flexibility, respectively (both ability scores: seconds per correct connection; max. time: 180 s for TMT A and 300 s for TMT B) [34, 35]. The Visual Memory Span from the German edition of the Wechsler Memory Scale-Revised [36] will serve to measure visuospatial working memory (working memory score: sum of points for forward and backward block tapping). Finally, we apply the Block Design subtest from the German edition of the Wechsler Adult Intelligence Scale-III to assess visuospatial reasoning (reasoning score: sum of points) [37].

The study assesses secondary visuospatial daily functioning outcomes both objectively and subjectively. The objective assessment of daily life functioning comprises three visuospatial subtests of the Timed Instrumental Activities of Daily Living (TIADL) [38, 39] (sub-scores: seconds for correct completion of task A - finding a telephone number*,* task B - making change*,* and task C - reading the list of ingredients on cans; objective daily functioning score: average of all three *z*-standardized sub-scores). Eleven visuospatial items of the Cognitive Failures Questionnaire will assess subjective function in everyday life (subjective daily functioning score: sum of points) [40, 41].

Self-report questionnaires will serve to assess secondary psychological outcomes. We will measure psychological well-being during the past 2 weeks with the World Health Organization (WHO)-5 Well-Being Index [42], general self-efficacy with the Generalized Self-Efficacy Scale [43], and perceived stress during the past month with the Perceived Stress Scale-14 [44].

We will use a 40-piece jigsaw puzzle (image: Rothenburg ob der Tauber by Ravensburger Spieleverlag GmbH (RSV); piece size: ca. 2.45 × 2.4 cm) to measure jigsaw puzzle skill. Thereby participants will complete the frame first and then the inner section of the puzzle (sub-scores for frame and inner section: seconds per connected piece; max. time for each task: 300 s; jigsaw puzzle score: average of both sub-scores).

In case of floor or ceiling effects (skewness ≥ 1 or ≤ − 1), we will use skewness minimization transformations (Blom transformations [45]) for all relevant ability scores and sub-scores. To increase measurement reliability and therefore the power of the study, the same psychologist will conduct pretest and posttest assessment of each participant, if possible. In addition, we will apply different methods to detect data entry errors, including range checks, plotting of pretest and posttest scores, and assessment of the retest-reliability for each score. Low retest-reliability of the primary outcome (*r* < .80) will result in double data entry.

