### Statistical analysis

The primary efficacy analysis will be based on mixed-effects models' group × time interaction [53] in an intention-to-treat approach [54] that includes all randomly assigned participants with follow-up observations. Effect sizes will include standardized differences in the pretest-posttest change scores between both groups. Standardization will be based on (1) baseline scores and (2) pretest-posttest change scores. In additional analyses, we will account for potential confounding variables such as baseline performance, the number of challenging social, physical, and cognitive activities performed in the past 4 weeks, the pretest-posttest change in these activities, Mediterranean diet in the past 4 weeks, and pre-posttest change in diet, age, education, participants’ test motivation at the posttest assessment, and their expectations of cognitive benefits.

As the primary intention-to-treat analysis is a conservative method, which may underestimate the true effect size of solving jigsaw puzzles for individuals who follow the protocol, we will use a supportive per-protocol analysis, which includes only participants who completed at least 80% of the jigsaw puzzle protocol (≥24 jigsaw puzzle days with a minimum of 45 min). With this supportive analysis, we do not only assess the robustness of effects, but may also receive a more accurate estimate of the true effect size given optimal conditions.

For subgroup and moderator analyses, pre-specified variables comprise baseline global visuospatial cognition, amount of lifetime puzzle experience, number of challenging social, physical, and cognitive activities within the intervention period, age, MMSE, and experienced pleasure in solving jigsaw puzzles.

Finally, we will assess cognitive demands of solving jigsaw puzzles and the transfer potential of gains in jigsaw puzzle skill on gains in the study outcomes by calculating the correlation between jigsaw puzzle skill in the 40-piece puzzle and the study outcomes at baseline.

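### The jigsaw skill score averages its two sub-scores in raw seconds per piece, so a Blom transformation of only one of them would mix scales and let the untransformed half dominate

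*Protocol article*

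**What the plan says.** All scoring rules at issue stand in the protocol article under Secondary outcomes.

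- Jigsaw sub-scores: "sub-scores for frame and inner section: seconds per connected piece; max. time for each task: 300 s". They are combined as "jigsaw puzzle score: average of both sub-scores".
- Mental rotation: "mental rotation score: average of both *z*-standardized sub-scores".
- Objective daily functioning: "objective daily functioning score: average of all three *z*-standardized sub-scores".
- In case of skewness of at least 1 or at most −1: "we will use skewness minimization transformations (Blom transformations [45]) for all relevant ability scores and sub-scores".

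The closing sentence under Primary outcome says that test scores are z-standardised on pretest values. It ends the definition of the eight-ability composite, of which the puzzle is not a part.

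The stated use of the jigsaw score is in Statistical analysis: the cognitive demands of puzzling and its transfer potential are assessed by "calculating the correlation between jigsaw puzzle skill in the 40-piece puzzle and the study outcomes at baseline". The Discussion relies on the same association to support the choice of outcomes.

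**The concern.** Three measures are built by averaging named sub-scores, and two of them standardise the parts first. A shared unit does not explain why the third does not: the two rotation sub-scores are both in seconds per correct item and the three daily-living sub-scores are all in seconds, yet both sets are z-standardised.

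Without a common scale, the weight of each half of the puzzle is set by its SD. The skewness rule adds a sharper problem. It is applied to single sub-scores, so one half can become a unitless normal score with SD 1 while the other stays in seconds. Their average has no clear meaning, and its weights depend on the unit in which time was recorded. Mental rotation and daily functioning are protected from this by standardisation; the jigsaw score is not.

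At stake is the reading of the baseline correlations between puzzle skill and the cognitive outcomes. They could describe mainly one half of the test, and a sample skewness near 1 could decide which half.

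**Working it through.** The protocol gives no mean, SD, skewness or correlation for the two sub-scores, so there is no figure of its own to reproduce. All numerical inputs below are assumptions.

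**1. Weight in an unweighted average.** Let k be the SD of one half divided by the SD of the other, and ρ their correlation. Then

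- correlation of the average with the half with the larger SD = (k + ρ) / √(1 + k² + 2ρk)
- correlation with the other half = (1 + ρk) / √(1 + k² + 2ρk)

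For k = 2 and ρ = 0.5 the root is √(1 + 4 + 2) = √7 = 2.646, giving 2.5/2.646 = 0.95 and 2.0/2.646 = 0.76.

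| k (ρ = 0.5) | larger-SD half | other half |
|---|---|---|
| 1 | 0.87 | 0.87 |
| 2 | 0.95 | 0.76 |
| 3 | 0.97 | 0.69 |
| 5 | 0.99 | 0.63 |

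**2. Neither half transformed.** Here k is the ratio of the two raw SDs, which is unknown. At k = 1 the halves weigh equally. Near-total dominance needs k of roughly 5 to 10.

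**3. One half Blom-transformed.** The transformed half has SD about 1, so k is simply the SD of the untransformed half in seconds per piece. The ratio of the raw SDs no longer matters. An SD of 2 s gives 0.95 and an SD of 3 s gives 0.97 with the untransformed half. The unit is decisive: an SD of 2 s is 2/60 = 0.033 min, and with k = 0.033 the correlation with the untransformed half drops to 0.533/1.017 = 0.52, while that with the transformed half is 1.0167/1.017 = 1.00. A score whose content changes between seconds and minutes is not well defined.

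Simulation with log-normal times (mean 5–8 s per piece for the frame, 8–20 s for the inner section, coefficient of variation 0.3–0.5, ρ about 0.5) agrees:

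| Transformed | Correlation with frame | Correlation with inner section |
|---|---|---|
| inner only | 0.92–0.98 | 0.61–0.78 |
| frame only | 0.53–0.71 | 0.96–1.00 |
| both | 0.82–0.85 | 0.82–0.85 |

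**4. How often this could happen.** Assume 22 frame and 18 inner pieces, the 300 s cap, n = 100, log-normal times with frame median 6–10 s and inner median 10–30 s, log-SDs 0.3–0.4 and 0.5–0.7, and 75% of each log sub-score's variance due to skill. Exactly one sub-score then meets the skewness rule in about 32–59% of samples, and the score correlates 0.97–1.00 with the untransformed half. Samples in which the inner section would dominate (no trigger, or frame only) make up about 0.5–13%.

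**5. What it costs.** Under the same assumptions, the score as written loses, against the z-standardised average, about 0.01 in correlation with true puzzle skill on average, up to about 0.04 when only one half is transformed, and 0.12 in the rare inner-dominated samples. If an outcome relates to the score only through skill, a loss of 0.04 from about 0.92 is 4%, so a correlation of 0.40 becomes about 0.38. Its sampling standard error at n = 100 is about (1 − 0.40²)/√100 = 0.08.

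**6. After the change.** With both halves at SD 1, each correlates √((1 + ρ)/2) with the score: 0.81, 0.87 and 0.92 for ρ of 0.3, 0.5 and 0.7.

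**The case against.** The strongest defence is that both jigsaw sub-scores come from one puzzle, in one unit, under one time cap, so a mean in seconds per piece is a legitimate and readable definition. The standardised measures combine more distinct tasks, and the rotation tests have different limits (90 s and 240 s). This stands as long as neither half is transformed. It fails once one is, because the shared unit is then gone.

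A second defence is that the Primary outcome sentence on standardising test scores already covers the puzzle. Its reach is unclear. If it covered sub-scores, the explicit wording for mental rotation and daily functioning would be redundant. If it covers only the finished jigsaw score, standardising after averaging leaves the weights as they were.

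Third, the article is condensed, and the full plan may settle how a conditional transformation is handled. That is possible, but the article does not leave the score open. It states a formula, and the formula works badly together with its own skewness rule.

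A reader might also infer stronger things that the document does not support:

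- *That the score in practice measures only the inner section.* This needs an SD ratio that is nowhere given, and under the assumed distributions the inner section usually meets the skewness rule itself.
- *That a one-sided trigger always leaves only the frame.* This holds in direction only if the inner section is the half transformed.
- *That the jigsaw score is the one multi-part score left in raw units.* It is not: see "episodic memory score: sum of the points in the immediate and delayed free recall trials" and "working memory score: sum of points for forward and backward block tapping". The contrast is with the other averaged sub-scores only.
- *That the least skilled participants would go unscored.* Seconds per piece is indeed undefined when no piece is connected, and mental rotation has a rule for the parallel case. Under the assumptions above, however, this affects at most 0.1% of participants.

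**Conclusion.** The point holds in a limited form. As written, the jigsaw score is not put on a common scale before averaging. A skewness trigger on one sub-score alone would then mix a unit-SD normal score with raw seconds and hand the score to the untransformed half, provided that half's SD is well above 1 s per piece. If both halves trigger, the problem disappears. If neither does, the half with the larger SD weighs more, by an amount that cannot be judged from the document.

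The effect is modest: about 0.01 on average in correlation with puzzle skill and up to about 0.04 with a one-sided transformation. These sizes rest on assumed log-normal times and an assumed equal dependence of both halves on skill. They could differ if an outcome relates to one half of the puzzle more than to the other.

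The only stated use affected is the supporting baseline correlation analysis and its interpretation in the Discussion. The primary outcome and its treatment comparison are unaffected.

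**What to change.** Under Secondary outcomes, define the jigsaw score as the mean of the frame and inner-section sub-scores after each has been z-standardised on its pretest mean and SD, with any Blom transformation applied first. This is the approach already taken for mental rotation and objective daily functioning.

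Optionally, carry over the mental rotation convention for the undefined case, so that a sub-score with no connected piece is set to twice the maximum time (2 × 300 = 600 s).

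The cost is one sentence and no new data. The downside is that the score is no longer in seconds per piece, so the raw sub-scores should be reported descriptively alongside it.

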#### Participants’ expectations

To account for potential effects of participants’ expectations regarding cognitive benefits of the interventions, we will assess these expectations within the last telephone call between week 3 and 4 after the start of the intervention (t_5_, see Figs. 1 and 2). Participants will be asked (1) whether they expect that their performance in the visuospatial cognitive tests has been influenced positively since the pretest (answers: “yes” or “no”), and (2) how much they expect their performance in the visuospatial cognitive tests to change from pretest to posttest assessment on a 5-point rating scale (answers range from “improve markedly” to “decline markedly”). We will use the same questions with respect to participants’ expectations of improvement in jigsaw puzzle performance.

#### Predictive variables of cognitive decline and dementia

The investigators will obtain the predictive socio-demographic variables age, gender, years of education, and main profession, using interview-based questionnaires. Three questions on the subjective degree of jigsaw puzzle experience on a 5-point rating scale (answers range from “very high” to “not at all”), the number of jigsaw puzzle hours, and the number of connected jigsaw puzzle pieces within participants’ lifetime will assess lifetime jigsaw puzzle experience. The assessment of risk factors for cognitive decline and dementia with self-rating questionnaires will include items on high blood pressure, hypercholesterolemia, diabetes mellitus, smoking, alcohol misuse, and obesity. The newly developed Challenging Leisure Activity Questionnaire is based on the CHAMPS Physical Activity Questionnaire for Older Adults [46] and will serve as a measure of the protective factors social, physical, and cognitive activities. Participants will indicate for each of 44 socially, physically, and cognitively challenging activities whether they performed them at least once during the past 4 weeks. A short 14-item Mediterranean diet questionnaire [47] will assess components of a Mediterranean diet. The measurement of risk and protective factors will serve as the basis for individual feedback in the cognitive health counseling and for the assessment of behavior changes between pretest and posttest assessments.

#### Adverse events

Non-blinded study staff will address potential adverse events at the beginning of the three telephone-based cognitive health counseling sessions (t_3_, t_4_, t_5_; see Figs. 1 and 2) and after completion of the posttest outcome measures.

### Interventions

Participants will be randomly assigned to one of two groups, the jigsaw puzzle group or the cognitive health counseling group (see Fig. 2). The jigsaw puzzle group will receive the 30-day jigsaw puzzle intervention and the cognitive health counseling, while the cognitive health counseling group will receive the cognitive health counseling only. We will ask the participants of the cognitive health counseling group not to solve any jigsaw puzzles within the 5-week intervention period. Participants of the cognitive health counseling group will receive a jigsaw puzzle after completion of the posttest assessments.

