## Methods

The Jigsaw *P*uzzles *A*s *C*ognitive *E*nrichment (PACE) study will take place at Ulm University, Germany, as a randomized, active-controlled, assessor-blinded superiority trial with two parallel groups. Between March and approximately October 2016, we will include and randomly assign 100 cognitively healthy, middle-aged and older adults (age 50 years and above) to a jigsaw puzzle group or a cognitive health counseling group with a 1:1 allocation ratio in blocks of four, stratified by cognitive status and age. Participants in the jigsaw puzzle group will engage in 30 days of solving jigsaw puzzles (6 days/week over a period of 5 weeks for at least 1 h/day) and receive cognitive health counseling (15-minutes face-to-face counseling plus three telephone calls). The cognitive health counseling group will receive the same counseling intervention but will not solve any jigsaw puzzles during the intervention period. The SPIRIT 2013 Checklist provides an overview about the contents of this study protocol (see Additional file 1).

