### Procedure

The Ethics Committee of Ulm University approved this study. We will invite individuals interested in participating in the study to a telephone-based interview. Here, they will receive detailed study information and give oral informed consent. A pre-screening will assess eligibility (t_1_, see Figs. 1 and 2). At an appointment at Ulm University, successfully pre-screened participants will be able to give written informed consent and will undergo further screening (t_2A_). For included participants, the procedure will consist of a 1.5-h pretest assessment composed of neuropsychological tests and questionnaires (t_2B_) followed by the face-to-face cognitive health counseling (t_2C_). Subsequently, non-blinded study staff will disclose the group allocation to the participants (t_2D_). Within 2 weeks after the baseline assessment, the 5-week intervention period will start. We will contact all participants three times via telephone for cognitive health counseling and the assessment of adverse events (AEs, t_3_ – t_5_). These telephone-based interviews will also serve to monitor the jigsaw puzzle experience and protocol adherence in the jigsaw puzzle group. Within 2 weeks after the intervention period, we will assess the same outcomes as in the pretest assessments in the 1.5-h posttest assessment at Ulm University (t_6_). Psychologists who are blind to group allocation will conduct the pretest and posttest assessments.

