
### Prevention of dropouts, noncompliance, and missing data

To ensure the application of the intention-to-treat principle, great effort must be invested to prevent dropouts, noncompliance, and missing outcome data, which introduce deviation from the randomization scheme [51, 52]. We will use different strategies including good personal contact through the telephone-based counseling; payment of 20€ for pretest and posttest assessments; communication of personal neuropsychological test results after the posttest assessments; interest in solving jigsaw puzzles and time commitment as study inclusion criteria; good availability of appointments for the pretest and posttest assessments (if appointments are not possible within the 2-week pretest and posttest period, we will arrange them as close as possible to this period); reminders for the posttest appointment at the last telephone-based counseling (t_5_); also if participants do not adhere to the intervention protocol, we will ask them to complete the posttest assessment; construction of a global ability score that allows some amount of missing data in the neuropsychological test battery; and prevention of excessive and insufficient mental demands through a large number of jigsaw puzzle difficulty levels (200 to 1500 piece puzzles; 2.8 × 3.0 cm to 1.8 × 1.7 cm piece sizes), adapted according to participants’ preferences, jigsaw puzzle experiences, and performance.

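### The controls' no-puzzle request covers only the 5-week intervention period, not the gaps of up to 2 weeks on either side before posttest (minor)

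*Protocol article*

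**What the plan says.** The restriction on controls appears twice in the protocol article, with the same window each time. The Interventions section says controls will be asked "not to solve any jigsaw puzzles within the 5-week intervention period". The opening of Methods says the counseling group "will not solve any jigsaw puzzles during the intervention period". No section extends the request to the posttest.

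The Procedure section sets the calendar. Group allocation is disclosed at t_2D, at the same appointment as the pretest and the face-to-face counseling. Then: "Within 2 weeks after the baseline assessment, the 5-week intervention period will start". At the other end: "Within 2 weeks after the intervention period, we will assess the same outcomes as in the pretest assessments". The section on dropouts and missing data loosens both windows without an upper limit: "if appointments are not possible within the 2-week pretest and posttest period, we will arrange them as close as possible to this period".

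Two further statements bear on the point. Eligibility requires "an interest in solving jigsaw puzzles", together with low puzzle experience in the past 5 years (fewer than five completed). The Interventions section gives controls their own puzzle only once the posttest is done.

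**The concern.** The primary outcome is change from pretest to posttest, so the contrast of interest is puzzle exposure against none over that whole interval. The request covers only the middle part of it. Controls know their allocation from the day of the pretest and were selected for an interest in puzzles and a readiness to spend an hour a day on them. They are also counselled that cognitive activities are protective. A control who buys a puzzle in the fortnight before posttest breaks no instruction.

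Any benefit such controls gain would raise the control mean at posttest and bias the group × time interaction toward zero. The primary analysis by randomised group cannot undo this. The per-protocol set in Statistical analysis is defined by completing the puzzle protocol, so it does not deal with controls who puzzle. Diaries and adherence monitoring are described for the puzzle group only. The activity questionnaire records whether each of 44 activities was done at least once in the past 4 weeks. The article does not show whether puzzles are on that list, and a yes/no item would not measure amount.

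Holding back the controls' puzzle until after posttest suggests that the aim is no puzzle exposure before then. The wording of the request is narrower than that aim.

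**Working it through.** **1. Length of the uncovered time**

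Inputs (Procedure): gap before the intervention 0 to 2 weeks; intervention 5 weeks; gap after it 0 to 2 weeks.

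- Pretest to posttest: from 0 + 5 + 0 = 5 weeks to 2 + 5 + 2 = 9 weeks, and longer if an appointment falls outside the windows.
- Not covered by the request: 0 to 2 + 2 = 4 weeks. At most 2 of these lie directly before posttest; the other 2 lie before the intervention starts.

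**2. What the other timing statements imply**

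- Participants' expectations puts the last call (t_5) between weeks 3 and 4 of the intervention, that is, about day 21 to 28.
- The blinding section puts that call about 9 days before the posttest. Posttest is then at about day 21 + 9 = 30 to 28 + 9 = 37, against an intervention end at day 5 × 7 = 35.
- Measures puts posttest about 5 weeks after baseline.

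On these figures the usual gap before posttest is about 0 to 2 days. They do not sit well with the wider windows in Procedure, and the interval statements should be reconciled.

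**3. The plan's own power**

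Inputs (Power analysis): 50 per group, 15% dropout, f = 0.1, r = .85, α = 0.05, stated power 90%. Analysed N = 100 × 0.85 = 85.

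For the within-between interaction with 2 groups and 2 time points:

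- λ = N × 2 × f² / (1 − r) = 85 × 2 × 0.01 / 0.15 = 11.33
- F test on 1 and N − 2 = 83 degrees of freedom: power 91.4%. With 84 analysed (42 per group) it is 91.1%.

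The stated 90% is reproduced to within 2 points.

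**4. Effect of dilution**

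If a share p of controls puzzles in the gaps and each gains a share g of the full effect, the contrast shrinks by p × g, and f becomes 0.1 × (1 − p × g). The article gives neither p nor g, so both are assumptions. For g, 2 weeks at 6 days a week is 12 of the 30 protocol days, so 12/30 = 0.4 if gain is proportional to days; 0.2 is half of that.

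| p | g | Dilution p × g | f | λ (N = 85) | Power |
|---|---|---|---|---|---|
| 0 | – | 0 | 0.100 | 11.33 | 91.4% |
| 0.10 | 0.2 | 2% | 0.098 | 10.88 | 90.3% |
| 0.10 | 0.4 | 4% | 0.096 | 10.44 | 89.1% |
| 0.20 | 0.4 | 8% | 0.092 | 9.59 | 86.5% |

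For dilution of 2% to 8%, the loss is about 1 to 5 percentage points.

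**The case against.** The strongest reply is that the gap will seldom matter:

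- By the article's own timing, posttest falls close to the end of week 5.
- Participants have completed fewer than five puzzles in 5 years, that is, under one a year; at that habitual rate a control would complete fewer than 5 × 2/260 ≈ 0.04 puzzles in 2 weeks.
- Controls get no study puzzle, catalogue or difficulty advice before posttest.
- The text is a journal article, and the exact instruction to participants may be wider in materials that are not shown.
- Any bias runs toward no effect, so it cannot create a false positive.

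Most of this stands, and it limits the size of the point. It does not remove it. Both statements of the restriction name the intervention period, the Procedure section expressly allows the longer gaps, and past habits are a weak guide for people who joined a puzzle trial and were allocated to no puzzles.

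A reader might go further and infer that 4/9 = 44% of the interval is open to puzzling just before posttest, that dilution will occur, or that power could drop to about 79%. The documents do not support this. Half of the 4 weeks precede the intervention, and dilution needs actual puzzle use, for which no rate is given. The 79% figure (84 analysed, f = 0.084) needs 40% of controls each to gain 40% of the effect, which is 16% dilution. If gain follows days, that means puzzling at the full protocol dose throughout a 2-week gap.

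**Conclusion.** The point holds as a minor one. As written, the restriction leaves up to 4 weeks of the pretest-posttest interval uncovered, at most about 2 of them directly before posttest under the stated windows and probably less in most cases. Control puzzle use in that time would be within the plan and could dilute the group × time contrast toward zero. Under an assumed dilution of 2% to 8%, power at the plan's own inputs goes from about 91% to between about 90% and 86%. That range rests on assumed values for the share of controls who puzzle and for what they gain. The direction of the bias matters mainly for how a null result would be read.

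**What to change.** - Word the request so that it runs from disclosure of allocation (t_2D) until the posttest assessment is completed, in both places where it is stated.
- Repeat it at t_5, with the reminders already planned for that call.
- After the posttest measures, when non-blinded staff already ask about adverse events, have them ask controls one question on any puzzle solving since pretest. Asked then and by those staff, it does not unblind the assessor.

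The cost is one changed sentence, one added reminder and one question, with no extra visit or staff. Controls refrain for up to about 4 more weeks under the stated windows, or longer if an appointment slips.
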